## Method of randomization and maintenance of blindness

All persons involved in the clinical trial (except those who performed the randomization assignment work for the investigational device) will be blinded to the randomization information in this trial.

The subjects enrolled in the study will be assigned to 2 groups (group A or group B) in a 1:1 ratio by block randomization on the Web. The total trajectory length at screening (<200 cm per 60 s, ≥200 cm per 60 s) and unilateral/bilateral vestibular disturbance will be assigned as the allocation factors. The allocation procedure will be conducted by the allocation manager appointed by the investigator in accordance with the "Procedure for Randomized Allocation of Investigational Devices" to be prepared separately. For Session I and Session II, the results of randomization of each subject in the registration system will be confirmed by a person other than the investigator (or subinvestigator) at the medical institution (called the Allocation Manager). The investigator will inform the Allocation Manager of the optimal intensity measured in the screening period, and the Allocation Manager will give the placebo stimulus or the device set to the optimal intensity (neither the subject nor the investigator can identify the placebo stimulus or the actual stimulus) according to the allocation result. The investigator or subinvestigator will play the set stimulus for 30 s and confirm that it is below the sensory threshold. As a method of confirmation, the patient is asked whether or not he/she perceives noisy GVS-specific stimuli (slightly spaced, continuous stimuli). If above the sensory threshold, continue to collect for subsequent data, but exclude from the main analysis (however, the data that have been measured up to that point can be used). If below the sensory threshold or above the sensory threshold, but the patient does not feel discomfort, the stimulus of that intensity is played continuously for 4 h. The patient is asked to stay in a designated place during the stimulation and not to touch the stimulating electrodes or the stimulator. We also check that the patient is below the sensory threshold at the time of measurement of the endpoints during stimulation, and if the patient exceeds the sensory threshold, we include the data up to the time before that point in the main analysis. The data obtained after the sensory threshold is found to have been exceeded will be used for supplementary analyses. The Allocation Director and the Allocation Manager shall keep the randomization allocation information confidential until the time of key opening.

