### Efficacy Analysis Methods

Primary analysis for the primary endpoint

The primary endpoint (percent change from baseline in total trajectory length) during stimulation (immediately after noisy GVS initiation to 3 h later) will be used as the response variable, and timing (Session I, Session II), treatment device (placebo, noisy GVS), time point, interaction between treatment device and time point, and allocation factors (total trajectory length at screening (per 60 s (<200 cm, ≥200 cm), unilateral/bilateral vestibular impairment) as the explanatory variables and fitting a mixed-effects model with individual effects as a variable effect. The least-squares mean of the treatment effect throughout the stimulation is calculated, and the *P* values are calculated for the 95% confidence interval and the null hypothesis that the treatment effect is 0%. The Kenward–Roger method is used to calculate the degrees of freedom.

　If the sensory threshold is found to be exceeded, a decision on whether to accept or reject the data thereafter will be made at the Case Review Committee.

The point estimates and 95% confidence intervals should be obtained for the least squares means of the rates of change by treatment device and time point calculated by the model above. The trends over time are also shown in the Figure.

Secondary analyses for the primary endpoints:

1. The descriptive statistics are calculated for the raw values of total trajectory length, change from baseline, and rate of change at all the time points by allocation group, treatment stimulus period, and time points. Subsequently, the allocation groups are combined, and descriptive statistics are calculated for each treatment device and time point. The descriptive statistics of the difference in the amount and rate of change within individuals are calculated for each time point, and a one-sample t-test is performed to calculate the *P*-value.
2. Corresponding t-tests will be performed for the difference between the mean rate of change in the total trajectory length from immediately after the start of stimulation to 3 h after stimulation in the GVS period and the mean rate of change in the total trajectory length from immediately after the start of stimulation to 3 h after stimulation in the placebo period.

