1. Descriptive statistics will be calculated for the percent change from baseline in the perimeter area and RMS values at all time points by allocation group, treatment stimulus period, and time point. Subsequently, the allocation groups are combined and descriptive statistics are calculated for each treatment device and time point. The descriptive statistics of the difference in the rate of change within individuals will be calculated at each time point, and a one-sample t-test will be performed to calculate the *P*-value.
2. For the rate of change in the total trajectory length, perimeter area, and RMS value in all time points, the mean rate of change and change over time in 95% confidence interval by treatment device and time point will be illustrated.

- Analysis of gait function tests

1. Descriptive statistics will be calculated for the percentage change from baseline in the gait test endpoints (DGI score, walking speed at 10-m gait, stride length, step time, and left-right sway) at all time points by allocation group, treatment stimulus period, and time point. Next, the allocation groups will be combined and descriptive statistics will be calculated for each treatment device and time point. The descriptive statistics of the difference in the rate of change within individuals at each time point will be calculated for each time point for the whole group and for each group, and a t-test between groups will be performed to calculate the *P*-value.
2. The same model as the main analysis for the primary endpoints will be used for the percent change in the perimeter area, RMS values, and gait test endpoints (DGI score, walking speed at 10 m gait, step length, step time, and left-right sway) during stimulation.
3. For the rate of change in endpoints of the gait test in all time points, the mean value of the rate of change and the changes over time in 95% confidence interval by device and time point shall be illustrated.

- Analysis for subjective improvement scores

1. Descriptive statistics will be calculated for subjective improvement scores at all time points by allocation group, treatment stimulus period, and time point. Subsequently, the allocation groups will be combined and descriptive statistics will be calculated by treatment device and time point.

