2. With the subjective improvement score during stimulation as the response variable; allocation group, treatment device, and interaction of time point as the explanatory variables; the mixed effect model with individual effect as the random effect is applied. The least squares means of the treatment effects throughout the stimulations is determined, and the 95% confidence intervals and *P*-values are calculated. The Kenward–Roger method is used to calculate the degrees of freedom.
3. For the subjective improvement scores in all the time points, the mean value and changes over time in the 95% confidence interval by treatment device and time point are illustrated.

- Analysis of QOL data

1. Descriptive statistics will be calculated for the change from baseline in the mFES score, DHI score, and DHI subscale scores at all time points by allocation group, treatment stimulus period, and time point. Subsequently, the allocation groups will be combined and descriptive statistics will be calculated by treatment device and time point. Regarding the difference in the amount of change within individuals, the descriptive statistics are calculated by time point and a one-sample t-test will be performed to calculate the *P*-value.
2. An analysis of covariance will be performed using the mFES score, DHI score, and DHI subscale scores at 3 and 7 h after the start of stimulation, respectively, as the response variables, and the allocation group, treatment device, and baseline values as the explanatory variables.

- Examination of correlations between endpoints

1. Pearson/Spearman correlation coefficients between the rate of change in total trajectory length at each time point during stimulation and the following variables are calculated for each treatment device.

- Percentage change in gait test endpoints
- Subjective Improvement Score

1. Pearson/Spearman correlation coefficients between the rate of change in total trajectory length and the following variables are calculated for each treatment device at 3 and 7 h after the start of stimulation, respectively.

- mFES Score
- DHI Score
- Scores for each subscale of DHI
- Number of steps
- Calculation of posterior probabilities

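### Gait item 1 compares the within-subject difference between the two sequence groups; if that difference is GVS minus placebo, the P-values test the session effect and not the device

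*Protocol*

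**What the plan says.** Protocol 12.2.4, analysis of gait function tests, item 1, first summarises the gait endpoints by allocation group, period and time point. It then pools: "Next, the allocation groups will be combined and descriptive statistics will be calculated for each treatment device and time point". Next comes the within-subject quantity: "The descriptive statistics of the difference in the rate of change within individuals at each time point will be calculated for each time point", reported "for the whole group and for each group, and a t-test between groups will be performed to calculate the" P-value. No one-sample test is named for gait.

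The item keeps two terms apart: *allocation group* for the sequence, and *treatment device* for GVS versus placebo. Section 10.3 says that subjects are "assigned to 2 groups (group A or group B) in a 1:1 ratio by block randomization on the Web". Group A receives GVS in Session I and placebo in Session II; group B receives the reverse.

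The sibling items in 12.2.4 test the same kind of difference in another way:
- Total trajectory length (secondary analysis 1 of the primary endpoint): differences "are calculated for each time point, and a one-sample t-test is performed to calculate the" P-value.
- Perimeter area and RMS: the "difference in the rate of change within individuals will be calculated at each time point, and a one-sample t-test will be performed".
- QOL scores: "the descriptive statistics are calculated by time point and a one-sample t-test will be performed to calculate the" P-value.

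Gait item 2 also applies the primary mixed model to the gait endpoints, but only during stimulation, which 12.2.4 defines as from immediately after the start to 3 h. Section 5.2 measures gait immediately after the start and hourly to 7 h.

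**The concern.** In a two-period crossover, a two-sample comparison of the sequence groups answers different questions depending on how the within-subject difference is formed. Taken as GVS minus placebo, it isolates the session effect. Taken as Session I minus Session II, it isolates the treatment effect. The gait item does not say which is meant, and its wording and its siblings point to the first.

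If so, the per-time-point P-values for DGI, walking speed, stride length, step time and sway width carry no information about the device. A practice effect between sessions, which is plausible for repeated gait tests, could be reported as a significant gait result. A true device effect would leave these particular P-values at the chance level.

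**Working it through.** The plan attaches no figure to this test, so there is none to reproduce. The check is algebra first, then an illustration.

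**Step 1: what the contrast estimates.** Let τ be the GVS-minus-placebo effect and π the Session I minus Session II effect, with no carryover.

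| Difference formed | Expected value in A | Expected value in B | A minus B |
|---|---|---|---|
| GVS minus placebo | τ + π | τ − π | 2π |
| Session I minus Session II | π + τ | π − τ | 2τ |

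In the first row τ cancels whatever its size. This needs no assumption about variance.

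**Step 2: which row the text implies.** The item reports the difference for the whole group as well as by group. Under 1:1 allocation, Session I minus Session II averaged over everyone is [(π + τ) + (π − τ)]/2 = π, which says nothing about treatment. GVS minus placebo averages to [(τ + π) + (τ − π)]/2 = τ. The one-sample tests in the sibling items also make sense only for GVS minus placebo. The first row is therefore the natural reading.

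**Step 3: how many P-values.** Five gait endpoints × 8 time points (immediately, then 1, 2, 3, 4, 5, 6 and 7 h) = 40. The mixed model in item 2 covers the time points up to 3 h. That leaves 5 × 4 = 20 (4 to 7 h) for which this t-test is the only frequentist test named.

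**Step 4: illustration of size.** Inputs:
- 40 completers (12.1.1), taken as 20 per sequence.
- 5% level (12.1.2), taken as two-sided.
- SD 30 and correlation 0.3, which 12.1.2 gives for trajectory length (the 0.3 is between time points). The protocol gives no gait SD and no between-period correlation, so both are assumptions here, with SD 15 to 30 and between-period correlation ρ 0.3 to 0.7 as the range.

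Formulae: SD of the difference = SD × √[2(1 − ρ)]. SE of the group contrast = SD of the difference × √(1/20 + 1/20). Noncentrality = 2π/SE, with 38 degrees of freedom.

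No GVS effect, π = 5 points, so the contrast is 10:

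| SD | ρ | SD of difference | SE | 10/SE | Chance of significance |
|---|---|---|---|---|---|
| 30 | 0.3 | 35.5 | 11.22 | 0.89 | 14% |
| 30 | 0.7 | 23.2 | 7.35 | 1.36 | 26% |
| 15 | 0.3 | 17.7 | 5.61 | 1.78 | 41% |
| 15 | 0.7 | 11.6 | 3.67 | 2.72 | 76% |

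**Step 5: simulation** (20,000 runs, 20 per group, one time point, SD 30, ρ = 0.3), rejection rates:

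| True GVS effect | Session effect | Between groups, GVS − placebo | One-sample, GVS − placebo | Between groups, Session I − II |
|---|---|---|---|---|
| 10 | 0 | 5.1% | 41.5% | 41.3% |
| 20 | 0 | 5.3% | 93.4% | 93.4% |
| 0 | 10 | 40.6% | 4.5% | 5.3% |

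Over the whole assumed range, with a true effect of 10 and no session effect, the between-group test on GVS minus placebo stays at about 5%, while the one-sample test rejects between 41% and 100% of the time.

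**The case against.** The strongest reply is that the protocol never writes GVS minus placebo. If Session I minus Session II is meant, a t-test between sequence groups is the standard period-adjusted test of treatment, and a by-group summary followed by a between-group test fits it. The English of this section is loose elsewhere, and 12 leaves analysis details to a separate statistical document. This stands in part: the wrong test follows from the natural reading, not from an explicit definition. It does not remove the point, because the whole-group summary and the sibling one-sample tests favour GVS minus placebo. As long as the direction is open, the sentence allows two tests with different targets.

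The second reply is that gait is analysed in other ways, and this stands. The mixed model in item 2 contains session and device, so it gives a valid period-adjusted comparison during stimulation. Posterior probabilities are planned for every secondary endpoint, patterned on an analysis of the data during stimulation. Item 3 plots means with 95% confidence intervals by device at all time points. A reader might infer that a real gait benefit would go undetected in this trial. The documents do not support that: only these t-test P-values are blind to it.

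A reader might also want one figure for the false-positive risk. The protocol supplies no gait variability, so only a range under stated assumptions is defensible. Section 11.3.6 has gait tests done only when possible, so 40 complete pairs may also be optimistic.

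**Conclusion.** The point holds in a limited form. The gait sentence names a test that departs, without a reason given, from the sibling items, and it leaves the difference undefined. If the difference is GVS minus placebo, as the context indicates, the 40 per-time-point gait P-values test the session effect. With carryover, the contrast would mix session and carryover effects and still would not estimate GVS versus placebo.

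The cancellation is exact. The 14% to 76% is illustrative: it assumes a 5-point session effect, 20 subjects per sequence, a two-sided 5% level and borrowed variability. The practical harm is greatest for the 20 P-values at 4 to 7 h, which serve the secondary objective on efficacy after stimulation ends. Up to 3 h a valid model-based test exists. These are secondary endpoints, and the primary analysis does not depend on this sentence. It should be corrected, but it does not threaten the trial's main conclusion.

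**What to change.** Rewrite the last sentence of gait item 1 in one of two ways.

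1. Define the difference as GVS minus placebo and apply a one-sample t-test at each time point, as for stabilometry and QOL. This is the smallest change and makes the section consistent. With unequal sequence groups its mean is τ + π(n_A − n_B)/(n_A + n_B), so a session effect enters in proportion to the imbalance.
2. Define the difference as Session I minus Session II, keep the t-test between groups A and B, and report half the contrast (2τ/2 = τ) as the treatment estimate. This adjusts for the session effect even when the groups are unequal. The whole-group summary should then be given separately as GVS minus placebo.

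Either way, state the direction of the difference and carry the same wording into the statistical analysis plan. The cost is one sentence: no new data, visits or subjects, and no change to the primary analysis.

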3. Inference on treatment effects using Bayesian flow methods: A mixed-effects model was fitted with the rate of change in the total trajectory length during stimulation as the response variable, the allocation group, treatment instrument, time point, interaction between treatment instrument and time point, and baseline values as explanatory variables, and individual effects as variable effects to obtain the posterior distribution of least squares means for the treatment effect. The prior distribution is Jeffrey’s uninformed prior distribution, and the posterior probability that the improvement in the GVS period is at least 5%, 10%, or 15% greater than the improvement in the placebo period is calculated. The 95% and 90% confidence intervals for the posterior probabilities are also calculated.
4. A mixed-effects model is fitted with the rate of change in the total trajectory length during stimulation in the GVS period as the response variable and baseline values as the explanatory variables to obtain a posterior distribution of the least-squares mean of the rate of change averaged over time points. The prior distribution is calculated as the posterior probability that there is at least 5%, 10%, 15%, and 20% improvement in the GVS period for the prior distribution obtained from Jeffrey’s uninformative prior distribution and the data up to 3 h after the second period of stimulation in the investigator-initiated clinical trial 3. The 95% and 90% credit intervals of the posterior probabilities will also be calculated.
5. To confirm the validity of the simulation experiment setting in the sample size estimation, correlation coefficients between the rates of change in the total trajectory length during stimulation will be calculated for each treatment device and time point.
6. The same model as in the main analysis for the primary endpoint will be used for the change from the baseline in the total trajectory length during stimulation.
7. The same analyses as the primary and secondary analyses (1) and (2) for the primary endpoint will also be performed using data after the sensory threshold is found to have been exceeded.

Analysis for secondary endpoints

- Analysis for Stabilometry

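### The QOL analysis of covariance omits the individual effect and the session, and the subjective-score and comparative Bayesian models list allocation group where the primary model has session

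*Protocol*

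**What the plan says.** All of the models concerned are in Protocol 12.2.4, Efficacy Analysis Methods.

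- **Primary model.** The terms include "timing (Session I, Session II), treatment device (placebo, noisy GVS), time point, interaction between treatment device and time point", plus the two allocation factors, and the plan specifies "fitting a mixed-effects model with individual effects as a variable effect". Session and subject are therefore both in the model.
- **QOL, item 2.** An analysis of covariance takes the mFES, DHI and "DHI subscale scores at 3 and 7 h after the start of stimulation, respectively, as the response variables", with "the allocation group, treatment device, and baseline values as the explanatory variables". No individual effect and no session are listed.
- **QOL, item 1.** The same scores also get a one-sample t-test by time point, introduced with "Regarding the difference in the amount of change within individuals". This analysis is paired.
- **Subjective improvement score, item 2.** The model has "allocation group, treatment device, and interaction of time point as the explanatory variables", with an individual random effect.
- **Comparative Bayesian model (secondary analyses of the primary endpoint, item 3).** It has "the allocation group, treatment instrument, time point, interaction between treatment instrument and time point, and baseline values as explanatory variables", again with individual effects. The paragraph on posterior probabilities carries this approach to each secondary endpoint.

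Allocation group means the randomised sequence A or B (section 10.3). It is not the session.

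**The concern.** Treatment device is a term in the QOL analysis of covariance, so each model must contain both sessions, and a completer supplies two rows. Without a subject term the model takes those rows as coming from different people. Section 6.2 justifies the crossover by the precision gained from comparing each patient with himself or herself; this one model gives that gain up. Allocation group is constant within a subject, so it restores neither the pairing nor an adjustment for session.

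The subjective-score and comparative Bayesian models have a narrower fault. They keep the subject effect, but with sequence in place of session they cannot remove a difference between Session I and Session II from the treatment contrast. At stake are the precision of one QOL analysis, its agreement with its paired companion, and an avoidable exposure to period effects in two supporting models.

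**Working it through.** **The plan's own figure.** The protocol states no precision or power for QOL. The only size figure concerns total trajectory length (section 12.1.2): 40/(1-0.20) = 50, and 50/(1-0.15) = 58.8, rounded up to 59 against a stated 60. I take only the 40 completers from it.

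**1. Missing subject effect in the QOL analysis of covariance**

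Inputs: N = 40 completers, split 20/20; outcome SD given baseline set to 1; residual correlation r between a subject's two sessions, assumed 0 to 0.7; two-sided 5% level (assumed); true effect 0.5 SD (assumed).

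- Variance that the model as written assigns to the treatment difference: 2/N = 0.05, so SE = 0.2236.
- Actual variance: 2(1-r)/N. At r=0.5 this is 0.025, so SE = 0.1581.
- SE ratio: 1/sqrt(1-r). At r=0.5: 1.41.
- Actual type I error: 2 x (1 - Phi(1.96/sqrt(1-r))). At r=0.5: 2 x (1 - Phi(2.77)) = 0.6%.
- Power as written: Phi((0.5 - 1.96 x 0.2236)/actual SE). At r=0.5: Phi(0.0617/0.1581) = Phi(0.39) = 65%.
- Power with the pairing kept: Phi(0.5/actual SE - 1.96). At r=0.5: Phi(1.20) = 88.5%.

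A simulation of the two-sequence crossover (3,000 replicates, no period effect, a separate baseline per session) gives slightly lower power for the paired model, because it uses t rather than normal critical values and estimates the extra terms:

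| r | SE ratio | Type I by formula | Type I simulated: as written / subject + session | Power simulated: as written / subject + session |
|---|---|---|---|---|
| 0 | 1.00 | 5.0% | 5.4% / 5.8% | 59.5% / 57.0% |
| 0.3 | 1.20 | 1.9% | 1.8% / 4.8% | 62.5% / 73.0% |
| 0.5 | 1.41 | 0.6% | 0.6% / 5.2% | 64.9% / 86.3% |
| 0.7 | 1.83 | 0.03% | 0.1% / 5.5% | 68.7% / 97.5% |

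**2. Session replaced by allocation group**

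Let p be the Session II minus Session I effect and t the treatment effect. Group A receives GVS in Session I, so its mean GVS-minus-placebo difference is t - p. Group B's is t + p. Averaged over subjects seen in both sessions, the estimate is t + p(nB-nA)/(nA+nB). A subject-level sequence term does not change this.

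With assumed p = 0.5 SD, t = 0.5 SD and r = 0.5:

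- 20/20: bias 0. The period effect still sits in the residual; in simulation, power with a subject effect but no session is 79.7%, against 85.9% with session, and type I error is 2.9% against 4.8%.
- 22/18: 0.5 x (18-22)/40 = -0.05, so the estimate is 0.45.
- 24/16: 0.5 x (16-24)/40 = -0.10, so the estimate is 0.40.

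With session in the model the simulated estimate stays at 0.50 in all three cases.

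**The case against.** The strongest reply is that the pairing is not lost from the QOL evaluation. Item 1 tests within-individual differences, and the Bayesian approach with individual effects extends to every secondary endpoint. This stands. A reader might infer that the crossover as a whole is analysed as two independent samples, or that a real QOL effect would be missed. The documents support neither: the description fits one analysis of covariance, and a paired test of the same scores is planned beside it. Item 1 has no session term either, so it shares the second fault but not the first.

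Second, r may be small. QOL is measured immediately before stimulation in each session (section 11.3.6), and that baseline may absorb much of the stable difference between subjects. At r=0 nothing is lost. This also stands, and is why the range starts at zero.

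Third, a reader might fear false QOL claims. For positive r the missing subject term pushes type I error below 5%, so it creates none.

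Fourth, dropout does not in itself unbalance the sequences. Allocation is 1:1 in blocks, and 20% dropout spread evenly leaves 20/20. Bias needs both a period effect and unequal sequences, and the protocol documents no period effect. In Table 8 the mean improvement is lower in Session III than in Session II at all five time points, but that is 13 patients, a different endpoint and untested, so it shows only that a session difference is conceivable.

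Finally, section 12 leaves details to a separate statistical document. That does not answer the point: the protocol lists the terms itself, and names the individual effect in its other two-session models but not in this one.

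**Conclusion.** The point holds in limited form. As stated, the QOL analysis of covariance is misspecified for a crossover. Its treatment standard error is too large by a factor between 1.00 (r=0) and 1.83 (r=0.7), it is conservative for any positive r, and it can disagree with the paired test in item 1 for a purely technical reason. The power figures rest on an assumed r, an assumed 0.5 SD effect and 40 completers in equal sequences.

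The subjective-score and comparative Bayesian models lack only the session term. The consequence is some lost precision if a period effect exists, and a bias of one tenth of that effect at 22/18 or one fifth at 24/16; there is no bias if the sequences stay balanced. The Bayesian analysis of the GVS period alone (item 4) makes no treatment comparison and is outside this point. The primary analysis already has both terms, and so do the perimeter area, RMS and gait analyses that reuse its model. All the affected analyses are secondary or supporting, so the correction is advisable but does not bear on the main conclusion.

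**What to change.** In 12.2.4, replace QOL item 2 with a mixed model for the mFES, DHI and DHI subscale scores at 3 h and at 7 h, containing an individual random effect, timing (Session I/II), treatment device and the session's own baseline. Add timing (Session I/II) to the subjective-score model and to the comparative Bayesian model, including where that model is carried to the secondary endpoints. Allocation group may stay alongside timing but should not stand in for it.

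The cost is a wording change in the protocol and in the matching part of the statistical analysis plan, made before the key is opened. No new data, visits or patients are needed, and the model form is the one already used for the primary endpoint.
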